**5. Dosing regimen**

When administering the drug, make sure that the "7-7-1. Dosing criteria" are met and that the "7-7-2. Dosing deferment criteria" and "7-7-3. Dosing discontinuation criteria" are not violated.

【Phase Ia】 Either 0.1 mg/kg, 0.5 mg/kg or 1.0 mg/kg is administered intravenously over 2 hours once a week for a total of eight doses.

【Phase Ib】 Either 0.1 mg/kg or 1.0 mg if tolerated up to 1.0 mg/kg in Phase Ia, either 0.1 mg/kg or 0.5 mg/kg if tolerated up to 0.5 mg/kg, or 0.1 mg/kg intravenously over 2 hours once a week for a total of 8 doses.

【Common to Phase Ia and Phase Ib】

1) Maintenance dose

The ninth and subsequent doses may be administered if the study drug meets the criteria for maintenance dosing described in 7-8, and maintenance dosing should be conducted every 4 weeks. Criteria for Drug Discontinuation".

2) Dosing interval

The dosing interval should not be shortened until eight doses have been administered. After nine doses, dosing may be postponed for up to two weeks and the next dose may be shortened by up to two weeks.

3) Pre-treatment at the time of administration

As reactions to injection are expected in almost all patients, diphenhydramine 30-50 mg and acetaminophen 300-500 mg should be taken internally 30 minutes before administration of the study drug. Hydrocortisone 100 mg is also administered intravenously pre-dose; after the second dose, diphenhydramine 30-50 mg and acetaminophen 300-500 mg are administered pre-dose. Drugs or doses may be changed or increased or decreased as appropriate according to age, symptoms and other factors.

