**6. Pre-treatment and concomitant therapy**

Confirm that no prior treatment (e.g., chemotherapy, radiotherapy) has been given for the target disease within 4 weeks prior to the start of the trial. For immunotherapy against tumors (e.g., tumor vaccines), confirm that no immunotherapy has been given within 12 weeks prior to case enrolment. Ensure that exclusion criteria are not violated.

Anticancer drugs, immunosuppressive agents (excluding steroids), immunoenhancing agents, radiotherapy and surgery for the primary disease (including metastasized tumors) are prohibited during the period of study drug administration. Corticosteroids may be administered locally or systemically as pre-treatment for the administration of investigational drugs and for symptomatic improvement of complications and adverse events.

Intravenous infusion of zoledronic acid or pamidronate and subcutaneous injection of denosumab for cases of bone metastases may be administered concomitantly once every four weeks if they were continued prior to participation in the study. However, administration on the same day as the study drug should be avoided.

The following vaccines should be used with caution.

1. Inactivated vaccines [may reduce the efficacy of vaccines (response to vaccination is unknown)].

2. Live or attenuated live vaccines [appropriate measures should be taken if symptoms based on the original disease of the live vaccine inoculated develop (response to vaccination is unknown and secondary infection by live vaccine cannot be ruled out)]. Treatment for other complications and adverse events should be available. Unapproved medicines and alternative therapies (e.g., folk remedies) are prohibited, but the use of food-like supplements is not prohibited.

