**8. Discontinuation criteria**

Dosing of the subject shall be discontinued if any of the following criteria are met.

1) When dosing is postponed for more than 2 weeks after the specified scheduled dosing date according to the dosing postponement criteria.

2) When "PD in overall efficacy in RECIST variant evaluation" is achieved after 24 weeks.

3) If an adverse event occurs that makes it difficult for the investigator to continue the study

4) If the subject requests discontinuation of the investigational drug

5) If the subject is found to be ineligible

6) Other cases in which the investigator decides that the trial should be terminated.

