**7-7. Dosing methods**

When administering the drug, ensure that the drug meets the "7-7-1. Administration Criteria" and does not conflict with the "7-7-2. Postponement of Administration Criteria" and "7-7-3. Criteria for discontinuation of administration”.

The investigational drug must be started within 2 weeks of case enrollment.

[Phase Ia] Either 0.1 mg/kg, 0.5 mg/kg or 1.0 mg/kg dose is administered intravenously over 2 hours once a week for a total of 8 doses.

[Phase Ib] If tolerability up to 1.0 mg/kg was confirmed in Phase Ia, 0.1 mg/kg or 1.0 mg/kg18

or 0.1 mg/kg or 0.5 mg/kg if tolerability up to 0.5 mg/kg is confirmed, or 0.1 mg/kg if tolerability up to 0.1 mg/kg is confirmed, administered intravenously over 2 hours once a week for a total of 8 doses.

[Common to both Phase Ia and Phase Ib]

1) Maintenance dose

The ninth and subsequent doses of the investigational drug will be administered every 4 weeks as maintenance doses, provided that "7-8. Criteria for Drug Discontinuation" are not violated.

2) Dosing Interval

The dosing interval should not be shortened until 8 doses have been administered. After the 9th dose, dosing may be postponed for up to 2 weeks, and the next dose may be shortened by up to 2 weeks.

3) Pre-treatment at the time of administration

Since reactions associated with injection are expected to occur in almost all patients, 30 to 50 mg of diphenhydramine and 300 to 500 mg of acetaminophen should be taken 30 minutes prior to administration of the study drug. In addition, 100 mg of hydrocortisone should be administered intravenously before the second dose of diphenhydramine 30-50 mg and 300-500 mg of acetaminophen after the first dose. Dosage may be adjusted according to age and symptoms.

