**7-7-2. Dosing deferral criteria**

Dosing of the investigational drug will be postponed if any of the following conditions occur on the scheduled dosing date^*1^. The period of postponement shall be a maximum of 2 weeks from the scheduled administration date.

1) Grade 4 or higher hematological adverse events. However, "febrile neutropenia" must be Grade 3 or higher.

2) Nonhematologic adverse events of Grade 3 or higher (excluding skin disorders). However, regarding laboratory tests, only those related to AST (GOT), ALT (GPT), ALP, total bilirubin, creatinine, and potassium should be considered.

3) In the case of ongoing skin disorders

4) If the subject requests a postponement of administration

5) Other cases in which the investigator determines that administration should be postponed

*1 Including within 3 days of the scheduled administration date as specified in the regulations.

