**7-7-3. Dose discontinuation criteria**

Dosing of the subject will be discontinued if any of the following criteria are met

1) When dosing is postponed for more than 2 weeks from the scheduled dosing date according to the criteria for dose postponement.

2) When "PD" is observed in the overall efficacy in the evaluation of RECIST variant after Week 24.

3) When a skin disorder of Grade 3 or higher is observed

4) Adverse events that make it difficult for the investigator to continue the study

5) The subject requests discontinuation of the investigational drug

6) The subject is found to be ineligible

7) Other cases in which the investigator determines that the study should be terminated.

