**7-9. Pre-treatment and concomitant therapy**

Confirm that no prior therapy (chemotherapy, radiotherapy, etc.) has been given for the subject's disease within 4 weeks prior to the start of the study. Immunotherapy (tumor vaccine, etc.) must not have been administered within 12 weeks prior to case enrollment. Confirm that there are no exclusion criteria.

Anticancer agents, immunosuppressive agents (excluding steroids), immunoenhancing agents, radiation therapy, and surgery for the primary disease (including metastasized tumors) are prohibited during the period of study drug administration. Corticosteroids may be administered locally or systemically as pretreatment for administration of the investigational drug or for symptomatic improvement of complications and adverse events.

Intravenous infusion of zoledronic acid or pamidronate and subcutaneous injection of denosumab for bone metastases are allowed if they have been administered once every 4 weeks if they were continued prior to participation in this study. However, they should not be administered on the same day as the investigational drug.

The following vaccines should be administered concomitantly.

1. Inactivated vaccines [may attenuate the effect of the vaccine (response to vaccination is unknown)].

2. Live or attenuated live vaccines [appropriate measures should be taken if symptoms based on the original disease of the live vaccine inoculated develop (response to vaccination is unknown, and secondary infection by live vaccine cannot be ruled out)]. Treatment for other complications and adverse events should be available. Unapproved drugs and alternative therapies (e.g., folk remedies) are prohibited, but the use of food-like supplements is not prohibited.

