**10-5-2. Skin disorder**

From the start of administration of this product, appropriate measures should be taken if any skin disorder is observed in collaboration with a dermatologist.

Since symptoms may progress rapidly and become severe in a short period of time, appropriate measures such as the use of a sufficient number of corticosteroids should be taken from the early stage of the onset of skin disorders. Corticosteroids should be considered for oral administration from the Grade 2 stage. Especially in cases of mucocutaneous disorders or when symptoms are ongoing, a sufficient dose (1 mg/kg prednisolone equivalent) should be used from the early stages of administration, and steroid pulse therapy should be administered in some cases.

If complications are observed, the skin disorder should be addressed while taking measures to deal with the complications.

If the skin disorder is ongoing, defer administration of the drug until the condition resolves.

If the skin disorder is Grade 2 or less and is controlled with corticosteroids at moderate doses (0.5 mg/kg prednisolone equivalent) or lower, consider continuation of the drug without deferral.

If Grade 3 or higher skin disorders occur, discontinue administration of the drug and take appropriate measures. Skin lesions caused by this drug may appear not only on visible areas such as the extremities, but also on the back, chest, and other parts of the body hidden by clothing. Also, since toxic epidermal necrolysis and Stevens-Johnson syndrome generally have mucocutaneous symptoms and may be preceded by mucocutaneous symptoms, the eyes, oral cavity, anus, vulva, and other skin-mucosal transition areas should also be checked.

Since severe skin disorders have been reported to occur not only during treatment with the drug but also several weeks after the end of treatment, patients should continue to be monitored regularly for their general skin condition after the end of treatment.

The recommended measures for each Grade are shown in Appendix 1.

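### For a persisting, steroid-controlled skin disorder of Grade 2 or less, the protocol's dosing rules (7-7-1 to 7-7-3) and its skin guidance (10-5-2) give incompatible instructions

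*Protocol*

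**What the plan says.** - **7-7-1** sets the condition for dosing: non-hematologic events may be up to Grade 2. It makes no separate provision for skin.
- **7-7-2** takes skin disorders out of its grade-based deferral rule (item 2) and gives them their own item: "3) In the case of ongoing skin disorders". The hold may last at most 2 weeks.
- **7-7-3** stops drug when a hold exceeds 2 weeks (item 1), and also "3) When a skin disorder of Grade 3 or higher is observed".
- **10-5-2** defers an ongoing skin disorder until it resolves and sets no limit. Its next sentence reads "If the skin disorder is Grade 2 or less and is controlled with corticosteroids at moderate doses (0.5 mg/kg prednisolone equivalent) or lower, consider continuation" without deferral. It discontinues at Grade 3 or higher and sends the reader to Appendix 1 for measures by grade.
- **Synopsis 8** has its own discontinuation list with no skin criterion. Its only adverse-event item is "3) If an adverse event occurs that makes it difficult for the investigator to continue the study". Synopsis 5, however, requires that 7-7-2 and 7-7-3 not be violated.

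Two other care instructions differ between synopsis and body. Synopsis 6 says of vaccines "The following vaccines should be used with caution", while 7-9 says "The following vaccines should be administered concomitantly". Synopsis 5 has "Hydrocortisone 100 mg is also administered intravenously pre-dose; after the second dose" the other two premedicants continue, while 7-7 has "100 mg of hydrocortisone should be administered intravenously before the second dose of diphenhydramine".

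**The concern.** Skin reactions are among the serious risks the protocol describes. Section 10-4 reports post-marketing toxic epidermal necrolysis and Stevens-Johnson syndrome, including a death. Sites need one instruction for each presentation.

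If two sites read different sections, the same rash leads to different exposure and different discontinuation counts. In Phase Ia it may also lead to a different DLT classification, and DLTs drive cohort expansion and the MTD. Such differences would come from the text rather than from the drug.

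**Working it through.** There is no planned figure to reproduce. The check sets the texts side by side for defined cases and then sizes the issue.

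**Case A: Grade 2 rash, still present on the dosing day, controlled on a moderate steroid dose**

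| Section | Instruction |
|---|---|
| 7-7-1 | Condition met; dosing permitted |
| 7-7-2 item 3 | Postpone, at most 2 weeks |
| 7-7-3 item 1 | Stop once the hold exceeds 2 weeks |
| 10-5-2, deferral sentence | Hold until resolved, no limit |
| 10-5-2, next sentence | Consider continuing without a hold |

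Section 7-7 requires 7-7-1 to be met and 7-7-2 and 7-7-3 not to be breached. Satisfying 7-7-1 is therefore not enough by itself, and within 7-7 the hold prevails. A site that uses the continuation sentence of 10-5-2 breaches 7-7-2 as written. A site that uses the open-ended deferral of 10-5-2 eventually meets the stopping rule in 7-7-3.

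**Case B: Grade 3 or higher.** 7-7-3 item 3 and 10-5-2 both discontinue. Synopsis 8 omits the criterion.

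**Appendix 1.** 10-5-2 cites it for measures by grade. Sections 2 and 12-2 cite Appendix 1 as the description of how the trial is organised. One number carries two contents.

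**DLT link (Phase Ia only).** Criterion 3(ii) in 8-3-1 counts a toxicity that prevents administration more than twice in the 28-day window through the same event. Weekly doses fall on days 1, 8, 15 and 22. Take a Case A rash present from day 8, with a causal link to the drug not ruled out:
- Held under 7-7-2 and still present on day 22: days 8, 15 and 22 are missed, so 3 > 2 and the criterion can be met.
- Dosed through under 10-5-2: 0 missed, so it is not met.

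This assumes that each missed weekly slot counts as one prevented administration, which the protocol does not spell out. A rash first present on day 15 blocks at most two slots (days 15 and 22) and does not meet it. Under 7-2, one DLT in three patients adds three patients, and three or more DLTs set the MTD.

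**Size.** Section 1-4 gives rash in 18 of 43 earlier patients: 18/43 = 41.9%, exact 95% interval 27.0% to 57.9%. If that rate applied here:
- Phase Ib group of 20: 20 × 18/43 = 8.4 patients with rash (5.4 to 11.6).
- Two groups, 40 in total: 40 × 18/43 = 16.7 (10.8 to 23.1).
- At least one rash in a Phase Ia cohort of 3: 1 − (25/43)³ = 80.3% (61.1% to 92.5%).

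**The case against.** The best counter-argument concerns the word ongoing. 10-5-2 calls for a sufficient steroid dose when symptoms are ongoing and then treats controlled disease separately. That fits a reading of ongoing as active or worsening. On that reading the section is tiered (stop, defer, consider continuing) and 7-7-2 item 3 would not reach a controlled rash. This stands as a possible reading, but the term is undefined and 7-7-2 carries no such exception. Even then, 10-5-2's open-ended deferral still conflicts with the 2-week limit.

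A reader might infer that Grade 3 rashes would go unstopped at a site working from the synopsis. The documents do not support that. Synopsis 5 and 7-7 both require compliance with 7-7-3, and 14-1-1 makes 7-7-3 the trigger for stopping. What remains is an incomplete list in synopsis 8.

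A reader might also take all 8 or so rashes per group as affected. The 18 of 43 include rashes that resolved between doses, uncontrolled rashes and Grade 3 or higher rashes, to which the Case A conflict does not apply. They also arose in patients with T-cell leukemia or lymphoma, and one Phase Ib group receives 0.1 mg/kg.

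A measures-by-grade table may well exist in an appendix not seen here. The point is only that the reference is ambiguous.

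Finally, the vaccine text in 7-9 introduces the same warnings as synopsis 6, so caution is the likely intent, and the hydrocortisone sentence in 7-7 looks like a translation fault. Both are secondary, but each still needs correcting.

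**Conclusion.** The point holds for a persisting skin disorder of Grade 2 or less that is controlled on a moderate or lower steroid dose. For it the protocol supports dosing, a hold of at most 2 weeks followed by a stop, or a hold without limit. It does not hold for Grade 3 or higher, where the operative sections agree.

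About 8 of 20 patients per Phase Ib group is a ceiling at the earlier rash rate. It assumes that the rate carries over to solid tumours and to these doses, and it counts rash only, whereas the rules speak of skin disorders in general.

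The effect on the DLT count is possible but not demonstrated. It is confined to Phase Ia, runs only through criterion 3(ii), and on the weekly schedule needs a rash that blocks all three remaining doses in the window. Non-hematologic toxicity of Grade 3 or higher that falls under criterion 2 is already a DLT.

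Because the conflict governs hold-and-stop decisions for a serious risk and is cheap to remove, it should be corrected.

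**What to change.** 1. Reconcile synopsis 8, 7-7-1, 7-7-2, 7-7-3 and 10-5-2 so that each skin grade and control status has one instruction, stated identically everywhere, including how long a hold may last.
2. Define *ongoing*.
3. Correct the Appendix 1 reference in 10-5-2 so that it points unambiguously to the measures by grade.
4. Secondarily, align the vaccine wording (synopsis 6 and 7-9) and the hydrocortisone premedication wording (synopsis 5 and 7-7).

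The clinical team decides which instruction stands in each case. The cost is protocol wording and a notice to sites; sample size and analysis are unchanged.

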**7-7-3. Dose discontinuation criteria**

Dosing of the subject will be discontinued if any of the following criteria are met

1) When dosing is postponed for more than 2 weeks from the scheduled dosing date according to the criteria for dose postponement.

2) When "PD" is observed in the overall efficacy in the evaluation of RECIST variant after Week 24.

3) When a skin disorder of Grade 3 or higher is observed

4) Adverse events that make it difficult for the investigator to continue the study

5) The subject requests discontinuation of the investigational drug

6) The subject is found to be ineligible

7) Other cases in which the investigator determines that the study should be terminated.

**7-8. Maintenance dose implementation criteria**

If all of the following criteria are met, maintenance dosing of the investigational drug to the subject concerned will be permitted until "7-7-3.

1) Maintenance dosing can be started within 6 weeks after the 8 doses.

2) If the subject shows an SD or greater in regulatory T-cell elimination and antigen-specific antibody immunoreactivity or RECIST after treatment with the investigational drug.

3) The subject wishes to receive maintenance dosing of the investigational drug

4) The investigator determines that maintenance administration of the investigational drug is appropriate.

**7-9. Pre-treatment and concomitant therapy**

Confirm that no prior therapy (chemotherapy, radiotherapy, etc.) has been given for the subject's disease within 4 weeks prior to the start of the study. Immunotherapy (tumor vaccine, etc.) must not have been administered within 12 weeks prior to case enrollment. Confirm that there are no exclusion criteria.

Anticancer agents, immunosuppressive agents (excluding steroids), immunoenhancing agents, radiation therapy, and surgery for the primary disease (including metastasized tumors) are prohibited during the period of study drug administration. Corticosteroids may be administered locally or systemically as pretreatment for administration of the investigational drug or for symptomatic improvement of complications and adverse events.

Intravenous infusion of zoledronic acid or pamidronate and subcutaneous injection of denosumab for bone metastases are allowed if they have been administered once every 4 weeks if they were continued prior to participation in this study. However, they should not be administered on the same day as the investigational drug.

The following vaccines should be administered concomitantly.

1. Inactivated vaccines [may attenuate the effect of the vaccine (response to vaccination is unknown)].

2. Live or attenuated live vaccines [appropriate measures should be taken if symptoms based on the original disease of the live vaccine inoculated develop (response to vaccination is unknown, and secondary infection by live vaccine cannot be ruled out)]. Treatment for other complications and adverse events should be available. Unapproved drugs and alternative therapies (e.g., folk remedies) are prohibited, but the use of food-like supplements is not prohibited.

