**9-3. Status of investigational drug administration and concomitant treatment**

1) Administration of investigational drug

The date and time of administration of the investigational drug should be noted in the case report form. If administration of the investigational drug is discontinued, the reason should be stated in the case report.

2) Status of concomitant treatment

For all concomitant medications and concomitant therapies administered to the subject from Week 1 to the time of completion or discontinuation of the investigational drug (4 weeks after the last administration), the daily dose, route of administration, start and end dates, and purpose of administration should be noted in the case report.

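### Section 7-9 tells sites to give inactivated and live vaccines alongside the study drug; the synopsis says to use the same vaccines with caution

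*Protocol*

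**What the plan says.** The protocol states its concomitant-therapy rules twice: in synopsis section 6 and in section 7-9 of the body. Both versions contain a short list with two entries, inactivated vaccines and live or attenuated live vaccines.

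- Synopsis section 6 opens the list with "The following vaccines should be used with caution".
- Section 7-9 opens it with "The following vaccines should be administered concomitantly".

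In 7-9 each entry carries a bracketed remark. The first reads "Inactivated vaccines [may attenuate the effect of the vaccine (response to vaccination is unknown". The second asks for appropriate measures if the disease behind a live vaccine develops, and gives as its reason "response to vaccination is unknown, and secondary infection by live vaccine cannot be ruled out".

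**The concern.** The two lead-ins do not say the same thing. One allows these vaccines with care; the other, taken at its word, is an instruction to give them with the study drug. The less safe wording sits in the body section, which is where a site would look for the operative rule.

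What is at stake is patient safety, mainly with live vaccines. The protocol itself documents why care is needed:

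- In the two earlier Japanese studies, which were in a different population (ATL and peripheral T-cell lymphoma), lymphocyte count fell in 41 of 43 patients, at Grade 3 or higher in 30 of 43 (section 10-4).
- Herpes zoster was a serious adverse event in the phase I study, and hepatitis B followed re-dosing in one patient (section 1-3-2-1). Section 10-4 does not rule out reactivation by the drug in that patient.
- Systemic steroids are part of management: hydrocortisone 100 mg as premedication (section 7-7), and prednisolone-equivalent 1 mg/kg or pulse therapy for skin disorders (section 10-5-2).

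**Working it through.** No arithmetic applies. The check is a comparison of the two texts.

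**Step 1. Are the lists the same?**

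| Element | Synopsis section 6 | Section 7-9 |
| --- | --- | --- |
| Lead-in | "The following vaccines should be used with caution" | "The following vaccines should be administered concomitantly" |
| Item 1 | "Inactivated vaccines [may reduce the efficacy of vaccines (response to vaccination is unknown" | "Inactivated vaccines [may attenuate the effect of the vaccine (response to vaccination is unknown" |
| Item 2, reason given | "response to vaccination is unknown and secondary infection by live vaccine cannot be ruled out" | "response to vaccination is unknown, and secondary infection by live vaccine cannot be ruled out" |

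The items match in order and meaning. The surrounding text also runs in parallel in both sections: the 4-week and 12-week washouts, the prohibited treatments, the steroid allowance, the bone-metastasis drugs, and the rule on unapproved medicines. Within the vaccine list, only the lead-in changes in force.

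**Step 2. Does 7-9 fit together by itself?** Its brackets say that the vaccine effect may be weakened, that the response is unknown, and that infection from a live vaccine is possible. These are grounds for restraint. They follow naturally from the synopsis lead-in and do not follow from an instruction to administer.

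**Step 3. Does anything else settle it?** The other mentions of vaccines concern tumor vaccines (the background in section 1-2, exclusion criterion 15, and the 12-week washout). None covers the inactivated or live vaccines in this list, and no written observation item in section 9 calls for vaccination. The schedule table is an image that is not shown, so it is not relied on here.

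**Step 4. Is this superseded or truncated text?** No. Both sentences are complete and stand in the current text.

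**Step 5. How much is affected?** One sentence. It governs 2 of 2 listed vaccine classes, and both carry a warning that the lead-in contradicts.

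**The case against.** The strongest reply is that this is a translation slip and not a planning error. The English text has others of the same kind. The heading of 10-1-2 states the reverse of its own definition of adverse reactions. The heading of 10-1-3 is garbled. The dose rationale in 7-1 says blood levels in solid tumors would be lower than in ATL and then that they may be higher. The premedication sentence in 7-7 is muddled where synopsis section 5 is clearer. The trial appears to be run in Japan, so sites may have worked from a Japanese text without the fault. The hazard is also contained: 7-9 names no vaccine, indication, dose or timing, and the warnings stand directly below the lead-in. A sensible clinician would not read it as an order.

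Much of this stands. A drafting or translation slip is the likely cause, though that is an inference. The documents do not show which language version sites held. The retained warnings do reduce the risk, and nothing in the inference changes.

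It does not remove the point. The source text is not available, and the protocol as supplied states one safety rule in two incompatible ways, with the weaker version in the body. Relying on each reader to notice that a lead-in contradicts its own list is a poor safeguard when the correction is one sentence.

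**Conclusion.** The contradiction is real and should be corrected. Section 7-9 is wrong as written: it conflicts with the synopsis and with the warnings it introduces. The synopsis wording is evidently the intended one, because it is the only lead-in that fits the list.

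The consequence is modest and confined to conduct and safety. The DLT rule, sample size, endpoint definitions and analyses are untouched. The number of patients exposed cannot be estimated, because the protocol gives no vaccination rate. The contradiction itself needs no assumption beyond reading the two sections as current text. That sites act on this English wording is not established, so the practical risk is conditional on that.

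**What to change.** Check the source-language text, then change the 7-9 lead-in to agree with synopsis section 6, for example: *The following vaccines should be used with caution when given concomitantly.* Leave both bracketed remarks as they are, and tell sites about the correction.

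The cost is one sentence in a protocol correction and a short note to sites. No new data collection is needed. Section 9-3 already requires dose, route, start and end dates and purpose "For all concomitant medications and concomitant therapies administered to the subject from Week 1" until 4 weeks after the last administration, so any vaccination in that period would be on record.
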